### Data collection

To investigate the effectiveness of NHGDoc, data will be collected from two sources: the NHGDoc server and Dutch Hospital Data.

#### NHGDoc server

For the largest part of this study, existing data collection methods from the NHGDoc alert service that have been developed by ExpertDoc to generate CDSS alerts for NHGDoc will be used. These are all automated data extractions from electronic patient records available in the EHRS. The NHGDoc alert service only uses anonymized patient data, and data are only streamed and not stored. For this evaluation study, however, it is necessary to save the anonymous data for the follow-up period of a year. Therefore, ExpertDoc, the company that manages the data, will send the NHGDoc data on a monthly basis, secured with a log in code, to IQ healthcare. NHGDoc data include all alerts, and the anonymous patient data that generate the alerts.

#### Dutch Hospital Data

To be able to detect the effects of NHGDoc on patient outcomes, we also use data from Dutch Hospital Data (DHD), a foundation that collects and manages data of Dutch hospitals. Based on the practice codes (practice AGB codes) of the participating practices in both arms, DHD selects relevant data with respect to hospital admissions and mortality of patients that are registered with ICD-code I50 of the ICD 10 and sends them, after anonymizing the dataset, to IQ healthcare.

### Analysis

To assess the effects of NHGDoc in terms of improving the quality of primary care, the scores on outcomes measures during the follow-up period will be compared between both study arms adjusted for baseline findings. To take into account potential clustering of effects within practices, multilevel models will be used.

The primary outcome measures are the percentage of consultations in which a patient with heart failure is prescribed 1. ACE-inhibitors/angiotensin II, 2. beta-blockers, and 3. diuretics. To assess the effects of NHGDoc on each of these variables, multilevel linear regression analysis will be performed. To assess the effects of NHGDoc on mortality, logistic regression analysis will be used, adjusting for severity of illness at hospital admission and comorbidity as measured by the Charlson Comorbidity Index. Both patient-level and practice-level intercept estimates will be used to account for potential correlation of measurements within patients and within general practices. We do not use the provider level estimates in our analyses as the difference between number of practices and providers will be too small due to solo practices. Moreover, patients may visit different GPs within the same practice during the year making this distinction less relevant as well.

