### Sample size

The minimum required number of general practices was based on the two main primary outcome measures: prescribing of ACE-inhibitors/angiotensin II and prescribing of beta-blockers. The anticipated improvement was based on literature [27,28] as well as on consultation of experts in the field (ACE-inhibitor change from 63%–69%; beta-blockers from 59%–65%). As for beta-blockers, to detect this difference, we will need at least 122 general practices completing the trial with 80% power at a type I error risk (*α*) of 5%, taking an estimated intra-cluster correlation of 0.1 into account [34]. With this number of practices, the study will also be able to detect the difference for prescribing of ACE-inhibitors (minimum number of practices =116). We do not, however, expect to be able to detect an effect on hospital admissions and hospital mortality with this number of practices.

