### Randomization

Eligible general practices will be randomly allocated to either the intervention arm or the control arm, stratified by type of EHRS (MicroHIS X or Promedico-ASP) (see Figure 1). Practices will be the unit of randomization. Before randomization, the practices will be clustered at the level of practice addresses (practice AGB code and zip code) to avoid GPs and practices that are located within the same building being designated to different study groups. Randomization will be central and computer-generated, executed by an independent person (one of the members of the research team without any COI towards allocation). Dedicated software will be used to generate a randomization scheme with an equal number of control and intervention practices.

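### Randomisation is stratified by EHR system, but the described model leaves that stratifier out; adding it is a free, low-severity improvement

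*Protocol article*

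**What the plan says.** The Randomization section of the protocol article states that "Practices will be the unit of randomization", that allocation is "stratified by type of EHRS (MicroHIS X or Promedico-ASP", and that the scheme gives "an equal number of control and intervention practices". EHRS is the only stratification factor.

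The Analysis section states that "the scores on outcomes measures during the follow-up period will be compared between both study arms adjusted for baseline findings". For the three primary prescribing percentages, "multilevel linear regression analysis will be performed". The random part is also given: "Both patient-level and practice-level intercept estimates will be used to account for potential correlation of measurements within patients and within general practices". For in-hospital mortality the section names covariates, "adjusting for severity of illness at hospital admission and comorbidity as measured by the Charlson Comorbidity Index". It also explains why no provider level is modelled.

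EHRS is not mentioned anywhere in that section, either as a covariate or as a stratum.

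**The concern.** Stratified allocation balances the two systems across the arms. The estimated difference between arms therefore no longer varies through chance imbalance in EHRS. A model without EHRS does not know this. It leaves the difference between systems in the practice-level variance, and so reports a standard error larger than the estimate's true variability.

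There is a plausible route for EHRS to matter here. Under NHGDoc server, the article says the process data are extracted automatically from records held in these systems. Recorded prescribing, and recorded creatinine, potassium, weight or blood pressure, may depend on how each system stores and sends data. The stake is modest: intervals slightly too wide and a little power lost on the prescribing and registration outcomes.

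**Working it through.** The plan gives no figure on this point to reproduce. Its sample size calculation contains no EHRS term, so adding EHRS does not change the stated 122 practices. The check asks how far the reported standard error (SE) is overstated when EHRS is left out.

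**Inputs from the article.** Two strata; equal allocation; intra-cluster correlation 0.1; effect sizes "ACE-inhibitor change from 63%–69%; beta-blockers from 59%–65" per cent; 122 practices.

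**Assumptions (not in the article).** Two strata of equal size; a two-sided 5% test; a practice-level linear model as an approximation to the multilevel one; the cluster size m; the correlation ρ between baseline and follow-up practice scores within a system; the share R² of practice-level variance due to EHRS; and the same EHRS difference in both years.

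**Case A: baseline adjustment works as planned.**

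Scale the variance of practice scores to 1. Ignoring EHRS, the baseline-to-follow-up correlation is r = ρ(1 − R²) + R². The residual variance is 1 − r² without EHRS and (1 − R²)(1 − ρ²) with it. Hence

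SE ratio = √[(1 − r²) / ((1 − R²)(1 − ρ²))].

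Example with ρ = 0.5 and R² = 0.10: r = 0.5 × 0.9 + 0.1 = 0.55, and the ratio is √(0.6975 / 0.675) = 1.016.

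The simulation used 122 practices allocated equally within two strata. The effect was set to give about 80% power when EHRS has no influence. That level is a yardstick, not an estimate of this trial's power. Paired entries are without / with EHRS.

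| ρ | R² | Formula ratio | Mean SE | True SD of estimate | Type I error | Power |
|---|---|---|---|---|---|---|
| 0.5 | 5% | 1.008 | 0.1543 / 0.1530 | 0.1545 / 0.1544 | 5.1% / 5.4% | 80.6% / 81.0% |
| 0.5 | 10% | 1.016 | 0.1515 / 0.1491 | 0.1500 / 0.1495 | 5.0% / 5.2% | 82.2% / 83.0% |
| 0.5 | 20% | 1.033 | 0.1451 / 0.1406 | 0.1402 / 0.1393 | 4.3% / 4.7% | 85.0% / 86.6% |
| 0.7 | 5% | 1.004 | 0.1269 / 0.1263 | 0.1272 / 0.1273 | 5.0% / 5.1% | 79.4% / 79.5% |
| 0.7 | 10% | 1.009 | 0.1239 / 0.1228 | 0.1244 / 0.1243 | 4.9% / 5.1% | 82.8% / 83.0% |
| 0.7 | 20% | 1.017 | 0.1181 / 0.1161 | 0.1160 / 0.1160 | 4.5% / 4.9% | 86.9% / 87.3% |

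The reported SE is about 0.5% to 3% too large, and power is 0.1 to 1.6 points lower. The true SD of the estimate is almost the same either way.

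**Case B: no useful baseline adjustment (outer bound).**

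The binomial variance, averaged over 59% and 65%, is (0.59 × 0.41 + 0.65 × 0.35) / 2 = 0.2347. With m = 47, the variance of a practice percentage is 0.1 × 0.2347 + 0.9 × 0.2347 / 47 = 0.0280. A difference d between two equal strata contributes d²/4. The SE ratio is 1/√(1 − R²), and the type I error is 2[1 − Φ(1.96 × ratio)].

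- d = 10 points: 0.0025 / 0.0280 = 8.9%; ratio 1.048; type I error 4.0%.
- d = 15 points: 0.005625 / 0.0280 = 20.1%; ratio 1.119; type I error 2.8%.

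Cluster size matters little. For m = 20 the ratios are 1.039 and 1.095; for m = 100 they are 1.053 and 1.132. On the same 80% yardstick, power without and with EHRS is 81.2% and 84.0% at R² = 10%, and 82.7% and 87.9% at R² = 20%.

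If EHRS explains nothing beyond baseline, the effect is nil in both cases.

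**The case against.** The strongest reply is that this is a condensed article. It does not define what its baseline adjustment contains, does not say that nothing else enters the model, and does not exclude EHRS. A full covariate list may stand in a document not shown. A reader might infer that the trial adjusts for baseline and nothing more, but the text does not support that; for mortality it names further covariates. What remains is that the section goes into detail on random effects, mortality covariates and the omitted provider level, yet the design's one stratifier does not appear in the model it describes.

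A second reply is that a stable difference between systems would already show in the baseline year, so baseline adjustment absorbs much of it. This stands, and it is why Case A is the main result. A reader might take the 5% to 12% inflation as the effect on the primary analysis. It applies only if baseline adjustment does little. The case is kept as a bound because the NHGDoc server section describes saving streamed data for the follow-up year and does not say how the baseline-year data are obtained. That is not evidence that baseline data are lacking.

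A third reply concerns scope, and it also stands. Mortality and system use might seem the outcomes most affected, since baseline adjustment is weakest there. But deaths come from Dutch Hospital Data rather than EHRS extraction, and they are analysed by logistic regression, to which the linear formula does not carry over. Exposure to NHGDoc is to be analysed descriptively, so no between-arm standard error is stated for it.

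**Conclusion.** The point holds as a free improvement of low severity. The allocation uses EHRS and the described model does not. Where EHRS is prognostic beyond baseline, the reported standard errors are conservative.

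Under the Case A assumptions, the SE is overstated by about 0.5% to 3% and the power loss is at most about 1 to 2 points. With weak or no baseline adjustment and a 10- to 15-point difference between systems, the SE is overstated by about 5% to 12%. The difference between systems, the baseline correlation, the cluster size and the equal strata are all assumed; the article gives none of them.

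Two stronger readings are not supported. The omission does not bias the effect or raise the false-positive rate, because the error runs in the conservative direction. Nor does it make the estimate itself materially less precise: stratification already balances EHRS, and the simulated spread of the estimate hardly changes. What suffers is the reported SE. Whether 122 practices suffice is a separate question and adds no weight here.

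**What to change.** State that EHRS (MicroHIS X or Promedico-ASP) enters as a fixed effect, alongside the baseline adjustment, in the between-arm models for the three primary prescribing outcomes and for the patient data registration outcomes. Naming it before analysis also removes a choice of model after the results are seen. According to Trial status, no data cleaning or analysis had been done at submission.

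The cost is one two-level covariate already known for every practice, and one degree of freedom. No new data and no change to the sample size are needed.

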#### Secondary outcome measures:

➢ Use of the system NHGDoc

Number of requests sent and alerts received for all patients; number of requests sent and alerts received for heart failure patients; percentage of opened alerts compared to the number received alerts; percentage of opened alerts compared to the number received alerts for heart failure patients; mean delivery time for an alert; number of practices that switched any module off; for each module, the number/percentage of practices with at least one user who switched the module off; and number of practices with at least one user who switched the module heart failure off (intervention group only).➢ Patient data registration

Percentage of consultations in which for a patient with heart failure, relevant patient data have been registered: clearance of creatinine (<12 mnd); (serum) creatinine (<12 mnd); (serum) potassium (<12 mnd); (serum) sodium (<12 mnd); patient weight (<6 mnd); heart (frequency) (<6 mnd); blood pressure (systolic and diastolic) (<6 mnd).➢ Hospital admissions

Number of hospital admissions of patients with heart failure.➢ All cause mortality

Number of patients with heart failure that died in the hospital.

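### The mortality model adjusts for severity at hospital admission, which exists only for admitted patients and arises after randomisation, and the outcome is headed all-cause although only in-hospital deaths of I50-registered patients are captured

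*Protocol article*

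**What the plan says.** All references are to the Protocol article.

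- **Analysis.** For mortality, "logistic regression analysis will be used, adjusting for severity of illness at hospital admission and comorbidity as measured by the Charlson Comorbidity Index". The section presents this model as the assessment of the effect of NHGDoc, not as a description of hospital case fatality.
- **Secondary outcome measures.** The outcome is headed "All cause mortality" and defined as "Number of patients with heart failure that died in the hospital". The outcome listed just before it is "Number of hospital admissions of patients with heart failure".
- **Data collection.** For effectiveness, "data will be collected from two sources: the NHGDoc server and Dutch Hospital Data". No death register is named.
- **Dutch Hospital Data.** Records are found through the practice codes in each arm: "DHD selects relevant data with respect to hospital admissions and mortality of patients that are registered with ICD-code I50 of the ICD 10". The foundation then "sends them, after anonymizing the dataset, to IQ healthcare".
- **Intervention arm.** The module is activated at trial onset. Heart failure was chosen partly because fairly large changes in mortality and morbidity are expected when guidelines are followed.
- **Sample size.** The outcome is called hospital mortality, and the authors do not expect to detect an effect on it or on admissions.

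**The concern.** A randomised comparison is protected when the people compared, and the covariates adjusted for, are fixed before the intervention can act on them. Here neither appears to be. Whether a heart failure patient enters the hospital file during follow-up, and how ill that patient is on arrival, are both settled after activation. Better prescribing in general practice could plausibly change either.

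If the module prevents admissions, the admitted patients in the two arms are no longer alike. If it makes presentations less severe, adjusting for severity takes that part of the benefit out of the estimate. Effects on patient outcomes are the second stated aim of the study, so the odds ratio would be reported as a treatment effect and read as one.

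Separately, a reader who sees an all-cause heading will assume that deaths at home or in a nursing home are counted. They are not.

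**Working it through.** The article states no mortality rate, effect size or event count, so there is no figure to reproduce. The check sets the sections side by side and then uses two illustrations with **assumed** inputs.

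**Step 1: who is in the model.** The covariate in Analysis is defined only for admitted patients. Deaths come only from hospital records with I50. The hospital file is anonymised, the server data are anonymous too, and no patient-level link between them is described. The risk set is therefore, by inference, admitted I50 patients. The article does not say so outright. The outcome, moreover, is defined as a number of deaths, while a logistic model needs a per-patient denominator that the definition does not supply.

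**Step 2: timing.** Activation comes at onset. Follow-up admissions and their severity come afterwards, and admission is a listed outcome. The selection and the severity covariate are both post-randomisation.

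**Step 3: label.** The heading covers any death. The definition covers deaths in hospital. The source covers patients registered with I50. Each is narrower than the one before.

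**Step 4: two-stratum arithmetic (assumed).** Each arm has 700 low-risk patients (10% admitted, 4% of those die in hospital) and 300 high-risk patients (30% admitted, 15% die). The module only prevents 30% of low-risk admissions.

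- Control: admissions 70 + 90 = 160; deaths 2.8 + 13.5 = 16.3.
- Intervention: admissions 49 + 90 = 139; deaths 1.96 + 13.5 = 15.46.
- Odds ratio over all 1,000 patients: (15.46/984.54)/(16.3/983.7) = 0.95.
- Odds ratio among admitted, unadjusted: (15.46/123.54)/(16.3/143.7) = 1.10.
- Within each stratum the risk of death once admitted is the same in both arms, so the odds ratio given stratum is 1.00.

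Full adjustment for stratum thus turns the misleading 1.10 into 1.00, but does not recover the 0.95. The benefit acts through admission, and a model of admitted patients cannot see it.

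**Step 5: simulation (assumed).** 2,000,000 patients; A is arm (0 or 1), U is standard normal unmeasured frailty, e is standard normal noise.

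- Admission: logit = −1.9 + 0.8U − 0.3A.
- Severity at admission: S = 0.7U + bA + 0.7e.
- In-hospital death if admitted: logit = −3 + 0.8S + 0.8U.
- Fitted model: logistic regression of death on A and S among admitted patients.

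| | Admission and severity lowered (b = −0.3) | Admission only (b = 0) |
|---|---|---|
| Admitted, control to intervention | 15.5% to 12.2% | 15.5% to 12.3% |
| Deaths per heart failure patient | 2.59% to 1.80% | 2.57% to 2.10% |
| Odds ratio, all heart failure patients | 0.69 | 0.82 |
| Odds ratio, admitted, unadjusted | 0.86 | 1.04 |
| Odds ratio, admitted, severity-adjusted (95% CI) | 1.18 (1.16 to 1.21) | 1.02 (0.99 to 1.04) |

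With an effect on admission only, the severity-adjusted model shows almost nothing although deaths per patient fell. When severity is lowered too, intervention patients with a given severity score are frailer than control patients with the same score, and the adjusted odds ratio passes 1. Both columns depend on the chosen coefficients.

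**The case against.** **The effect on admission and severity is only possible, and perhaps small.** This stands. The anticipated prescribing shift is 6 percentage points. Assume a drug cuts admissions by 10% to 50% in newly treated patients. A 6-point shift then cuts admissions by about 0.6% to 3% per drug (0.06 × 0.10 to 0.06 × 0.50). Putting cuts of 2% to 6% into the low-risk stratum of Step 4 gives unadjusted odds ratios among admitted of about 1.01 to 1.02, against 0.997 to 0.990 over all patients. The distortion is small there, but so is the effect to be estimated. This tempers the magnitude and leaves the logic as it is.

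**A reader might infer that the planned estimate will point the wrong way.** The documents do not support that. A simple example in which mild admissions are prevented puts the odds ratio above 1 only without adjustment. The plan adjusts for severity, and in Step 4 that returns the odds ratio to 1.00. Reversal under an adjusted model needed further assumptions: an effect on severity and unmeasured frailty.

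**A reader might also fault the patient-level intercept, since death occurs at most once.** The intercept sentence in Analysis is general. The text that follows it, on patients seeing different GPs during the year, fits the repeated-consultation outcomes. Nothing ties the patient intercept specifically to death.

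**Charlson comorbidity.** No case is made here that chronic comorbidity lies on the path from the module to death. The objection concerns severity at admission and the restriction to admitted patients.

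**The label is only wording, since the definition sits directly beneath it and all-cause may mean any cause of death.** Fair in part: the scope is disclosed. The heading still promises more than the data source can hold.

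**The risk set is inferred and detail may sit in a fuller plan.** True, but the severity covariate is stated in the article, and it restricts any model that uses it to admitted patients.

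**Conclusion.** The concern holds in a limited form. As written, the effect on mortality is estimated with a covariate that exists only for admitted patients and that, in follow-up, arises after the module is active, while admission is itself an outcome. The result would be a case-fatality comparison among admitted I50 patients, not a randomised comparison of mortality. It may hide or distort an effect acting through admission or severity. How far, and in which direction, cannot be derived from the article; the odds ratios above show only what is possible under assumed inputs.

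The conclusion rests on one inference, that the model is fitted among admitted patients, and on one possibility, that the module changes admission or severity. The mismatch between heading and definition needs neither.

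Mortality is secondary and power is expressly disclaimed, so the primary prescribing conclusions are unaffected. Low power does not make the estimate interpretable as an effect, so the plan should be changed before analysis. Trial status says that no cleaning or analysis had been done at submission.

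**What to change.** 1. Rename the outcome as in-hospital mortality of I50-registered patients.
2. Make the main analysis the number of in-hospital deaths per practice in the follow-up year, compared by arm with Poisson or negative binomial regression. Account for the randomised unit, bearing in mind that practices are grouped by address before randomisation. Adjust for the baseline-year count and other pre-randomisation covariates only, such as the EHRS stratum.
3. Add a pre-randomisation practice-size offset if one is available. This has to be confirmed: server data arise when a patient file is opened, are not normally stored, and are saved for the follow-up year, and list size is not mentioned. A denominator built from files opened after activation would itself be post-randomisation.
4. Keep the severity- and Charlson-adjusted logistic model as a descriptive case-fatality analysis among admitted patients, not as an effect estimate, and report it beside the admission counts by arm.

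Cost: a changed analysis paragraph and a new outcome name. No new data are needed for the count with baseline adjustment, because outcomes are already to be measured in the year before the intervention. The hospital file must keep a coded practice identifier, which the planned practice-level intercept needs anyway. The downside is that the main mortality result is no longer a case-mix-adjusted odds ratio, and without an offset practice size is reflected only through the baseline count.
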